## Method

### Design

This study is a single-center, randomized controlled trial using a waitlist control condition assessing the first implementation of LPP in China. The objective of this study was to preliminarily explore the effectiveness and feasibility of LPP in addressing parenting stress among Chinese parents.

The study will be conducted at a comprehensive hospital in Guangzhou, China. Parents who are enrolled in the study will participate in a 5-week LPP intervention. Parents will be asked to complete self-report questionnaires and to participate in a follow-up at 3 months and 9 months after study inclusion. The study flow is illustrated in Figure 1.

**Figure 1 F1:**
[figure not shown]
Expected flow of participants from recruitment through to the end of the study.

### Recruitment

The subject recruitment strategy employed in this study is multifaceted, encompassing targeted referrals, publicizing lectures, printed advertisements (flyers and posters), and social media. Potential participants will be furnished with pertinent information, including a link to the program profile and an enrollment link. All parents will be required to contact the project team through self-enrollment.

### Inclusion and exclusion criteria

The study further aims to examine whether the LPP, in addition to reducing parenting stress, may exert a preliminary preventive effect on children's mental health risk. As the optimal age for prevention falls below 14 years, this cutoff was applied. To balance heterogeneity of developmental characteristics, measurement coverage and feasibility of parental participation, the child age range was set from 4 to 14 years. Eligible participants are parents of children aged 4 to 14 years experiencing elevated parenting stress, defined as a Parenting Stress Index (PSI) score ≥ 85 (critical high level) with informed consent. Exclusion criteria included: (1) serious physical illness (e.g., cancer), (2) active severe mental illness, and (3) communication difficulties or language barriers that would prevent meaningful participation in a group-based intervention.

### Sample size

The determination of these parameters was facilitated by the utilization of the PASS 15.0 (NCSS Statistical Software, East Kaysville, UT, USA) software. Preliminary studies in the field have indicated a decline in the values of the indicators—total stress of PSI in the LPP intervention group, with a mean decrease of 11.3, and a corresponding decrease in the control group, with a mean decrease of 3.1 based on a previous MBT-based early intervention study (Fonagy et al., 2016). The experimental design employed a parallel approach, with the groups assigned in a 1:1 ratio. Given the exploratory nature of this study and resource constraints, a relatively liberal alpha level of 0.1 was adopted for sample size estimation. The clinical threshold of non-inferiority was set at 10% and the power level was set at 0.8. PASS15.0 calculated a total of 20 cases for each group. In the preparatory phase for this RCT, a pilot trial was conducted with a small cohort of five parents. As a zero dropout rate was observed in this pilot, no oversampling to compensate for participant attrition was deemed necessary. However, based on attrition rates observed in a comparable Chinese trial and accounting for the waitlist-control design, we conservatively estimated an attrition rate of approximately 10% (Jiang et al., 2024). Consequently, a minimum total sample size of 44 participants (22 per group) was determined to be required.

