### Primary research questions

To evaluate the potential efficacy of the randomized controlled trial (RCT), the primary research questions focus on changes in parenting stress:

Do parents in the TI group report a greater reduction in parenting stress index (PSI) scores following the 5-week intervention, compared to those in the WL group?

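### The sample size rests on a 10% non-inferiority threshold, but the primary question is superiority over a waitlist, so the 80% power is not shown to be that of the primary comparison

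*Protocol article*

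**What the plan says.** Under Primary research questions, the protocol article asks: "Do parents in the TI group report a greater reduction in parenting stress index (PSI) scores following the 5-week intervention", compared with the waitlist group. The Design section describes a "randomized controlled trial using a waitlist control condition". Statistical analysis names repeated measures ANOVA, t-tests and chi-squared tests.

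The Sample size section builds the calculation from these elements:

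- Mean PSI total changes: "with a mean decrease of 11.3, and a corresponding decrease in the control group, with a mean decrease of 3.1".
- Allocation: "with the groups assigned in a 1:1 ratio".
- Significance level: "a relatively liberal alpha level of 0.1 was adopted for sample size estimation", justified by exploratory aims and limited resources.
- Margin and power: "The clinical threshold of non-inferiority was set at 10% and the power level was set at 0.8".
- Result: "PASS15.0 calculated a total of 20 cases for each group", raised to 22 per group (44 in total) for attrition of about 10%.

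The paragraph does not say what the 10% is a percentage of. It also gives neither the SD of change nor the sidedness of alpha.

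**The concern.** A non-inferiority threshold belongs to a trial that asks whether one treatment is not unacceptably worse than another. This trial asks whether treatment is better than waiting. Its comparator is a waitlist, and its planned tests address a difference from zero.

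The mismatch affects the power statement. Under non-inferiority the null hypothesis is that treatment is worse than control by at least the margin. With a true benefit, that null lies further from the truth than the null of no difference, so the same sample rejects it more often. If the software was given the margin as the sentence describes, the 80% is the power for a hypothesis that the trial never tests, and the power for the primary question is lower. This paragraph is the article's only statement of power for the primary outcome, and the Discussion's description of the sample as the minimum necessary relies on it.

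**Working it through.** **Inputs from the Sample size section.** Mean decreases 11.3 and 3.1; 20 per group; power 0.8; alpha 0.1; threshold 10%.

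**Assumptions, because the article does not give them.** A common SD of change in both groups; alpha either one-sided or two-sided; the margin in PSI points.

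**Step 1: expected difference.** 11.3 − 3.1 = 8.2 points.

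**Step 2: can 20 per group be reproduced?** Not forwards, since no SD is given. It can be solved backwards. For a two-sample t-test with n per group, df = 2n − 2 = 38, the noncentrality is d × √(n/2) with √(20/2) = 3.162, and power is the noncentral-t probability beyond the critical value. Solving for 80% power with n = 20 gives:

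- two-sided 0.10 (critical t 1.686): d = 0.80
- one-sided 0.10 (critical t 1.304): d = 0.68
- two-sided 0.05 (critical t 2.024): d = 0.91

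**Step 3: if no margin was used.** SD = 8.2 / d.

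- two-sided 0.10: 8.2 / 0.801 = 10.2
- one-sided 0.10: 8.2 / 0.679 = 12.1

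So 20 per group matches a plain superiority calculation only at one of these SDs.

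**Step 4: if the margin was used as worded.** The software would be powering a distance of 8.2 + margin. The implied SD is (8.2 + margin) / d, and the superiority effect is then 8.2 / SD. Candidate margins are 10% of the control change (0.31), of the difference (0.82) and of the treatment change (1.13). Worked example with 0.82, two-sided 0.10: SD = 9.02 / 0.801 = 11.3; superiority d = 8.2 / 11.27 = 0.728; power 73%.

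| Margin (points) | Implied SD, two-sided 0.10 | Superiority power | Implied SD, one-sided 0.10 | Superiority power |
|---|---|---|---|---|
| 0 | 10.2 | 80% | 12.1 | 80% |
| 0.31 | 10.6 | 77% | 12.5 | 78% |
| 0.82 | 11.3 | 73% | 13.3 | 74% |
| 1.13 | 11.7 | 71% | 13.7 | 72% |

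The superiority power is at the same alpha as the SD column to its left.

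**Step 5: dependence on the unstated SD.** Superiority power for 8.2 points with 20 per group:

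| SD | Two-sided 0.10 | One-sided 0.10 | Two-sided 0.05 |
|---|---|---|---|
| 10 | 82% | 90% | 72% |
| 12 | 68% | 80% | 56% |
| 15 | 52% | 67% | 39% |
| 20 | 36% | 50% | 24% |

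**The case against.** The strongest reply is that the article does not show how, or whether, the threshold entered the software. If the term is a slip and the calculation was two-sided at 0.10 with an SD near 10.2, then 20 per group does give 80%. The threshold might even be a mislabelled superiority margin, subtracted rather than added. With 10% of 8.2 taken off, the implied SDs are 9.2 and 10.9, and power against a zero difference would be 87% (two-sided 0.10) or 86% (one-sided 0.10). The text neither states nor excludes that reading. This stands, and it means the 80% cannot be called wrong, only unverified for the primary comparison. It does not rescue the sentence, which under either of these readings misdescribes what was done.

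Other replies also stand:

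- Alpha 0.1 is disclosed, called liberal and justified, so it is a choice and not an error.
- The SD, the sidedness and the significance level of the primary test may sit in a fuller protocol or analysis plan that is not shown. Their absence from an article is not a fault in itself.
- The Discussion presents the trial as a small pilot whose findings are preliminary and need replication, so no confirmatory claim depends on the 80%.

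**Conclusion.** The point holds as a contradiction on the page: a non-inferiority threshold sizes a trial whose question, comparator and planned tests all concern superiority. The consequence is that 80% power with 20 per group is not shown to be the power of the primary comparison. If the threshold was used as worded, with a base of 10% of the quoted changes or of their difference, superiority power is about 71% to 78% at alpha 0.10, a modest shortfall. If it was not used, 80% holds only for an SD of change near 10.2 or 12.1, depending on sidedness.

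A reader might infer more than this, without support from the document:

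- **That power is drastically low.** Taking 10% of the PSI entry cut-off of 85 gives a margin of 8.5 points and superiority power of only 34% (two-sided 0.10) or 41% (one-sided 0.10). Nothing links the threshold to the cut-off, and that margin exceeds the whole expected difference of 8.2.
- **That the primary test will be run at 0.05, so that 80% fails for that reason.** The article sets no significance level for the analysis; its silence is not a decision.
- **That a null result would be read as evidence against the programme.** The stated limitations advise caution.

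Confidence is high on the contradiction and limited on the size of any power loss, because the SD, sidedness and base of the 10% are assumptions. The point should be fixed; it does not invalidate the design.

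**What to change.** Remove the non-inferiority threshold. Restate the calculation as a two-group superiority comparison of T0-to-T1 change in PSI-SF total, giving the SD and the sidedness actually used. State that the primary test uses the same alpha as the sample size.

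Keep N = 44 and report what it delivers. With about 10% attrition, 22 × 0.9 = 19.8, or about 20 evaluable per group. That gives 80% power for a standardised difference of about 0.80 at two-sided 0.10, 0.68 at one-sided 0.10 or 0.91 at two-sided 0.05. A short table of power for 8.2 points over a range of SDs would let readers judge it.

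The cost is one rewritten paragraph and no extra participants. The downside is that the stated power may become less favourable.

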### Randomization

Randomization will occur immediately following the completion of baseline assessment. Eligible participants will be assigned in a 1:1 ratio to either the immediate intervention group or a waitlist control group using a computer-generated sequence with random block sizes of 4 and 6. Stratification was not performed given the exploratory nature of the study and the anticipated sample size. An independent data manager generated the allocation sequence, and participant enrollment was conducted by a clinical interviewer, who then accessed a secure web-based system to obtain the treatment assignment. Baseline comparability between conditions will be examined on key demographic and clinical variables. Participant blinding is not feasible, as individuals must be informed whether they will begin the intervention immediately or after a 2-month delay.

### Intervention

The lighthouse parenting programme (LPP) implemented in this study is a revised version developed by the Institute for Psychosocial Prevention, University Hospital Heidelberg (Taubner et al., 2019), consisting of five weekly group sessions and five accompanying individual sessions. Group sessions form the core of the intervention, introducing key mentalization-based treatment (MBT) concepts—such as mentalization, emotional triggers, autopilot behavior, and intergenerational transmission of attachment—through metaphors drawn from a sea voyage. These sessions foster reflection, shared understanding, and collaborative problem-solving around parenting challenges. Individual sessions are integrated with group content and tailored to each parent's needs, offering focused exploration of personal patterns in parenting and the influence of their family of origin. Parents are supported in observing and mentalizing their own and their child's behaviors, while developing strategies for change and resource access. Group sessions are facilitated weekly by a consistent, experienced psychotherapist, who also delivers the individual sessions. The 5-week program delivers one group and one individual session per week.

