### Data collection procedure

Subsequent to enrollment and the provision of informed consent, parents will be invited to the site where the intervention will be administered to participate in the questionnaire assessment and interview on-site (T0). Parents eligible to participate will then be randomly assigned to either the treatment immediate group (TI) or the waitlist control group (WL). Participants in the WL group were offered to participate in the intervention after a 2-months observation period. During this 2-month period, TI group received the full intervention and completed the posttest at the conclusion of this period. Prior to the WL intervention, participants in both groups will receive a second questionnaire assessment (T1). Subsequent to the WL's completion of the intervention, a third questionnaire assessment will be conducted (T2). At subsequent follow-ups, both groups will continue to complete two assessments (T3 and T4) at 3- and 9-months post-intervention.

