### Statistical analysis

All parents assessed at baseline (T0) will be included in the data analysis following intent-to-treat principles. Sociodemographic variables and baseline assessment data will be used to characterize the enrolled sample. Descriptive data on recruitment, dropout, and retention rates will also be collected. Additionally, qualitative data—including reasons for dropout—will be analyzed to evaluate the appropriateness and acceptability of the study procedures and intervention. The primary objective of this study is to examine changes in participant's parenting stress and other parenting-related correlates (e.g., parental mentalizing, personality functioning, self-efficacy, and mental health), parent-child relationship quality, and children's variables (e.g., child's behavior difficulties and temperament) before and after the intervention, measured by standardized questionnaires. Participant satisfaction will be assessed using a standardized questionnaire. Furthermore, parents' subjective experiences during the LPP will be explored through semi-structured interviews. The quantitative data will be analyzed using SPSS 21.0 (IBM Corp., Armonk, NY, USA), employing repeated measures ANOVA (rmANOVA), *t*-tests, and chi-squared tests. The analysis of qualitative data will be conducted using the grounded theory methodology.

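### If outcomes correlate within therapy groups, the planned tests understate the standard error of the T1 comparison, because only the TI arm is treated in groups

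*Protocol article*

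**What the plan says.** All places are in the protocol article.

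- **Randomization.** Individual parents are allocated 1:1, without stratification, "using a computer-generated sequence with random block sizes of 4 and 6".
- **Intervention.** TI parents receive five weekly group sessions and five individual sessions. "Group sessions form the core of the intervention, introducing key mentalization-based treatment (MBT) concepts". On staffing: "Group sessions are facilitated weekly by a consistent, experienced psychotherapist, who also delivers the individual sessions". The number and size of the groups are not given.
- **Data collection procedure.** "Prior to the WL intervention, participants in both groups will receive a second questionnaire assessment (T1". The WL arm is therefore untreated when the primary comparison is made.
- **Statistical analysis.** The quantitative analysis is described as "employing repeated measures ANOVA (rmANOVA), *t*-tests, and chi-squared tests". No term for group or therapist is mentioned.
- **Sample size.** 20 per arm, raised to 22 per arm (44 in total) for about 10% attrition. No ICC or design effect appears. On the level, "a relatively liberal alpha level of 0.1 was adopted for sample size estimation".
- **Discussion, limitations.** Small sample, child age range and self-report are covered. Clustering is not.

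**The concern.** This is a partially nested design: individual randomisation, one arm treated in groups, the other not. Parents who work through problems together for five weeks share a leader, a group climate and each other's influence, so their later scores may be more alike than those of unrelated parents.

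The named tests cannot reflect that. Repeated measures ANOVA handles the correlation between one parent's own measurements, not the correlation between parents. With only T0 and T1 in the model, its arm-by-time test is equivalent to a t-test on change scores, so any shared group effect arising after T0 enters the treatment contrast directly.

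The primary research question is a between-arm comparison of PSI change. If the standard error is understated, the interval is too narrow and evidence for LPP is overstated. With 44 parents, a modest shift can decide whether a result is called positive.

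**Working it through.** **The plan's own figure.** The 20 per arm cannot be reproduced, because no SD is given and the 10% margin has no stated base. The assumed difference is 11.3 − 3.1 = 8.2 PSI points. Read as a simple comparison of means with alpha 0.10 and power 0.80, n = 20 implies an SD of about 10.4 (two-sided) or 12.2 (one-sided). The step from 20 to 22 is 20 × 1.1, so attrition uses up the whole addition and nothing is left for a design effect.

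**Inputs.** From the article: 22 parents per arm, groups in TI only, tests assuming independence. Assumed, because the article gives neither: ICC from 0 to 0.10, and 22 TI parents in four groups (6, 6, 5, 5), three (8, 7, 7) or two (11, 11). The only hint on size is the five-parent pilot cohort. The ICC is that of whatever outcome is tested, here change in PSI.

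**Formulas.**
- Design effect in TI: DE = 1 + (m − 1) × ICC, with m = Σmᵢ²/Σmᵢ for unequal groups.
- Variance ratio of the arm difference: (DE + 1)/2, since WL is unclustered and the arms are equal in size.

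**Example at ICC 0.05.**
- Four groups: m = 122/22 = 5.55, DE = 1.23, variance ratio 1.114, true SE √1.114 = 1.055 times the naive SE.
- Three groups: m = 162/22 = 7.36, DE = 1.32, variance ratio 1.159, SE factor 1.077.
- Two groups: m = 11, DE = 1.50, variance ratio 1.250, SE factor 1.118.

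**Type I error of the ordinary two-sided t-test** (simulation, 100,000 runs per scenario, random group effect in TI only, equal total variance). Each cell gives the true level at nominal 0.05 / nominal 0.10.

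| ICC | Four groups | Three groups | Two groups |
|---|---|---|---|
| 0 | 0.050 / 0.099 | 0.050 / 0.101 | 0.051 / 0.100 |
| 0.01 | 0.052 / 0.103 | 0.053 / 0.104 | 0.056 / 0.109 |
| 0.05 | 0.063 / 0.118 | 0.069 / 0.127 | 0.080 / 0.142 |
| 0.10 | 0.078 / 0.138 | 0.088 / 0.153 | 0.112 / 0.184 |

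The row for ICC 0 returns the nominal levels, as it should. If all 22 TI parents formed a single group, ICC 0.05 would give 0.114 / 0.185, and no model could estimate the group variance.

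**Sample size.** If 20 per arm is right under independence, the number needed for 80% power before dropout is 20 × (DE + 1)/2. Groups of 5: 20 × 1.10 = 22 at ICC 0.05 and 20 × 1.20 = 24 at ICC 0.10. Groups of 10: 20 × 1.225 = 24.5 and 20 × 1.45 = 29.

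**Can the data estimate the ICC?** Hardly. At a true ICC of 0.05, the between-group mean square falls below the within-group mean square in about 48% of trials with four groups, 50% with three and 56% with two (F distribution, equal group sizes). A REML variance held at zero then returns essentially the unadjusted result.

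**The case against.** The strongest reply is that harm is not shown. The excess needs a positive ICC, which the article does not give. At ICC 0.01 with groups of 5-6 it is negligible (0.052 against 0.05). The five-parent pilot points to small groups, and half of the sessions are individual. The trial calls itself a pilot awaiting replication, and an analysis plan that is not shown could add a group term. Most of this stands as a limit on size. It does not remove the point: the tests the article names cannot carry a group effect, and pilot status is no reason for an interval that is too narrow.

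Four stronger readings are tempting but unsupported:

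- **That false positives will exceed the nominal level.** This follows only if outcomes correlate within groups.
- **That the trial tests at 0.10, so the inflation adds to a loose level.** That alpha is stated for sample size estimation only. No level is set for the analysis, so the figures at nominal 0.10 are illustrative.
- **That a single therapist causes the clustering.** The wording can mean one therapist per group or one for the whole trial. If one person treats every TI parent, that effect is confounded with LPP. It is then a limit on interpretation, not a within-arm correlation that these tests mishandle.
- **That two parents of one child may enrol and add dependence.** The eligibility criteria do not exclude it, but nothing suggests that it is expected, and an article may leave such a rule to the full protocol.

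**Conclusion.** The point holds in conditional form. The design is partially nested at T1, the named analyses and the sample size treat parents as independent, and nothing in the article corrects for this. The standard error of the TI-WL difference is understated to the extent that outcomes correlate within groups.

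Over ICC 0.01 to 0.10 and 2 to 4 groups, the true level of a nominal 0.05 test runs from about 0.05 to 0.11, and of a nominal 0.10 test from about 0.10 to 0.18. These figures rest on the assumed ICCs and group sizes and on equal total variance in the two arms. The structure described is that of T1. After T2 the WL parents will have been treated as well, so later comparisons need their own treatment of grouping. The matter should be addressed before analysis, but it does not invalidate the trial.

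**What to change.** 1. Record a therapy-group identifier for every treated parent, and report the number and size of groups.
2. Alongside the primary PSI comparison at T1, report the interval and p-value with the TI-arm variance multiplied by 1 + (m − 1) × ICC at fixed ICCs, for example 0.01, 0.05 and 0.10. This should lead, because it does not depend on estimating the ICC from very few groups.
3. If TI is run in several groups, also fit a partially nested mixed model: a random group effect in TI only and small-sample degrees of freedom. State that 2 to 4 groups estimate the ICC poorly and that a single group does not identify it.
4. List group clustering among the limitations. State how many therapists deliver LPP and, if one treats all TI parents, that the therapist effect cannot be separated from the programme's.

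The cost is an identifier the team already knows and some extra analysis. Recruitment and treatment do not change. The downside is a wider interval and a less favourable p-value.
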